### Data collection

For the primary outcome sickness absence, data will be collected from the SSIA and self-reported short-term sickness absence will be collected weekly from the participants as described above.

For the secondary outcomes, an email is sent to the patient with a link to the questionnaire where the patient-reported data will be collected using the self-administrated instruments at inclusion (baseline), at one and 3 months after inclusion (short-term follow-up), and at six and 12 months after inclusion (long-term follow-up). Data on age, gender, location of birth, education, family, present employment or source of income, and symptom duration will be collected at inclusion. The patient drawing of the pain sites marked on an anatomical sketch of a human body is sent out separately by mail and returned in a pre-paid envelope. A reminder is sent by email once per week during 4 weeks, to promote participant retention and complete follow-ups. For the patient drawing, one reminder is sent out after 2–3 weeks by mail. If a patient wishes to withdraw from the study or further follow-ups, he or she is asked to approve the collection of registry data from SSIA and the Swedish registry for drug consumption.

Data on interventions received in both the PREVSAM and the TAU group will be collected from the participant’s electronic medical record, which also will be used for monitoring of intervention adherence/treatment fidelity. The interdisciplinary teams are instructed to report on solicited and spontaneously reported adverse events and other unintended effects of trial interventions or trial conduct. Any concomitant interventions provided for the same diagnosis will be collected via Region Västra Götaland’s healthcare utilisation database (VEGA).

Outcome data from the web-based questionnaire will be transferred to a database, where it will be checked for accuracy by the research assistant to promote data quality.

There will be no data monitoring committee since the study is independent from the sponsor and the intervention consists of a rehabilitation model that includes evidence-based treatment methods with little risk for unexpected adverse events.

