### Outcomes

#### Primary outcome

##### Sickness absence

Sickness absence will be measured using the proposed outcome measures from the Swedish Social insurance report 2016:9 [31]. These measures are based on sick-leave data at the individual level (including diagnoses) of all sick-leave spells longer than 14 days in which sickness cash benefits were provided by the SSIA. Data will be retrieved from the MiDAS database (preventive sickness absence will be excluded as this might be part of intervention). All sickness absence is planned to be analysed, but the main focus is on sickness absence relevant to musculoskeletal pain. Sickness absence was chosen as primary outcome because it is a frequent consequence of musculoskeletal pain, and it is of relevance for both the individual, the employer and society to measure and target this outcome when testing and implementing a new rehabilitation model for this patient group.

Sickness absence will be operationalised as:
Number and proportion of individuals who were on sickness absence and/or the number and proportion of individuals who remain in full- or part-time work during the follow-up period.Number of gross and net sick-days during the follow-up period.Time to first sickness absence spell.

Short-term sickness absence (≤ 14 days) is not reported to the SSIA among employed participants. They have sick pay from their employer the first 2 weeks of a sick-leave spell. Thus, short-term sickness absence will be measured using self-reported responses to weekly text messages via mobile phone (SMS-Track ApS, Denmark, www.sms-track.com). The participants will enter a number from 0 to 7 in response to the question “Have you been absent from work during the past week due to your musculoskeletal pain, and if so for how many days?”. However, unemployed participants have sickness benefits from the SSIA from the second day of a sick-leave spell.

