##### Drug consumption

Consumption of pharmaceutical drugs that can be related to the musculoskeletal condition for which the participant is treated (ATC codes M – musculoskeletal system and N – nervous system) will be estimated using data from the Swedish registry for drug use, regarding filled prescriptions. Data will be collected for a 3-month period before baseline and for the 12-month period after baseline. Self-reported drug consumption, both prescription and nonprescription drugs, will be collected via the questionnaire.

Other secondary outcome measures are loss of productivity and healthcare costs and incremental cost-effectiveness ratios [17].

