Group characteristics will be presented as mean and standard deviations, median and 25th and 75th percentile or the number and percentage. For the primary outcomes descriptive analyses for sickness absence for the two groups will be presented according to recommendations [31]. The sickness absence will be presented with number of individuals who had sickness absence during the follow-up period. Proportions of individuals with sickness absence per month will be presented. The number of sick days (gross and net) with sickness benefit during the follow-up periods will be presented with mean and median values. For participation in work life additional measures will be presented with descriptive statistics regarding time to sick-leave spell for musculoskeletal pain. Number of days before a sick leave spell > 14 days occurs and number and duration of sick-leave spells per individual will be presented for gross and net days. Outcomes will be analysed according to intention-to-treat. Multivariable logistic regression analysis will be used for the primary outcome sickness absence during the follow-up period [1], not being sickness absent (0) adjusted for confounders. Multivariable linear regression analyses, or possibly quantile regression, will be used to evaluate differences between groups for sick leave days, among those have at least one sick leave spell. All other measurements will be analysed by calculating raw differences between baseline and follow-up assessments. Parametric and non-parametric tests will be used depending on data level and distribution. Sub-group analyses can be performed in regard to characteristics of interest, such as diagnosis or sick-leave. The level of significance is set to *p* < 0.05. Relevant statistical programs will be used for the statistical analyses, for example the IBM SPSS, SAS, STATA.

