### Ethical considerations and data management

Even though the intervention does not include any new technology per se, but rather a more comprehensive, yet focused, rehabilitation model, several ethical issues need to be considered. Screening for a condition can sometimes be controversial. There might be a risk that we find too many cases and “overtreat” these people. However, if the study does not find any benefits of the new model, we will have a clear indication that there is no need to introduce this more comprehensive model at an early stage.

There is also a possibility that people are hesitant about healthcare professionals approaching and collaborating with their employer. However, clinical experience has shown that people often perceive that the healthcare system can be a legitimate channel to reach the employer to explain the needs, and also to stress the responsibilities of each part.

Eligible participants who meet the inclusion criteria and preliminary agree to participate, will receive oral and written information, including the written consent form, by a healthcare professional at the study centre, before or at their first visit to the clinic. The information includes that participation is voluntary and that they may withdraw participation at any time, without any consequences for their continued treatment or rehabilitation. If the patient accepts participation, he/she returns the signed informed consent to the study centre and these are collected by the project coordinator. The informed consent can also be sent back by mail to the project coordinator. In the informed consent the participants also consent to collection of registry data.

The study will involve collection and management of personal demographic and outcome data, which will be treated with high respect for the persons’ integrity. All collected data will be coded and a code list will be created, giving the possibility to go back and double check raw data. Data and code list will be stored separately and will only be accessible by authorised members of the research team, as will the final trial dataset. Data will be managed according to Swedish law and in compliance with Region Västra Götaland’s data management guidelines. This includes registry with the Data Protection Officer of Region Västra Götaland and storage in a locked and fireproof safe and on access-controlled servers with high levels of security.

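### Participants who only stop texts or questionnaires are asked to re-approve register data they consented to at entry, which puts the register-based primary outcome at avoidable risk of being missing

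*Protocol article*

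**What the plan says.** Under Ethical considerations and data management, the Protocol article states: "In the informed consent the participants also consent to collection of registry data". It also lets participants withdraw at any time.

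Under Data collection, the rule for leavers reads: "If a patient wishes to withdraw from the study or further follow-ups, he or she is asked to approve the collection of registry data from" the SSIA and the drug register. The two situations share one sentence and one procedure. Nothing is said about what happens if the person declines or gives no answer.

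The outcomes concerned come from registers. For sickness absence, the primary outcome, "Data will be retrieved from the MiDAS database", which holds the SSIA's benefit data. Drug consumption "will be estimated using data from the Swedish registry for drug use, regarding filled prescriptions". Under Statistical analyses, "Outcomes will be analysed according to intention-to-treat". Under Blinding, neither patients nor treating professionals are blinded.

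**The concern.** A register-based primary outcome can be obtained for almost everyone randomised, however many people tire of weekly texts and e-mailed questionnaires. That protects an intention-to-treat analysis, and the rule in Data collection weakens it. A person who wants only the messages to stop is asked for an approval already given, and so is offered an occasion to refuse something they had not asked to end.

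If some refuse, their 12-month sickness absence is missing although no one set out to revoke consent for it. Patients know their allocation, so the wish to stop could depend on arm. It could also depend on how the patient is doing. The documents give no evidence on either point. The drug-register outcome is exposed in the same way. Self-reported short-term absence necessarily ends when the texts stop, so for these people the registers are the main outcome source left.

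**Working it through.** **1. The two provisions side by side.**

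| Situation | Entry consent to register data | What Data collection asks |
|---|---|---|
| Stops texts or questionnaires only | Still stands | New approval for SSIA and drug register |
| Leaves the whole study | May be in question | New approval for SSIA and drug register |

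In the second row the question has a clear purpose. In the first row it asks for what is already held.

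**2. The plan's own sample size.** Inputs from Statistical analyses: 30% absence in controls, 15% in the intervention group, 80% power, α = 0.05 (two-sided assumed), 132 per group, 200 per group randomised after allowing for dropouts. With p̄ = 0.225:

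n = [1.96·√(2·0.225·0.775) + 0.842·√(0.30·0.70 + 0.15·0.85)]² / 0.15² = 121 after rounding up.

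A continuity correction raises this to 134, against 132 stated. The same method gives 313 for 30% against 20%, against 312 stated. The plan's figure is reproduced to within two patients per group.

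**3. Power if register outcomes are lost at random.** Power = Φ{[0.15·√n − 1.96·√(2·0.225·0.775)] / √(0.30·0.70 + 0.15·0.85)}, without continuity correction. The loss rates are assumed.

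| Lost per group | n per group | Power |
|---|---|---|
| 0% | 200 | 95.1% |
| 5% | 190 | 94.1% |
| 10% | 180 | 92.9% |
| 20% | 160 | 89.9% |
| 34% | 132 | 83.5% |

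The last row is 1 − 132/200 = 34%. With the continuity correction that the plan appears to use, 132 per group sits at about the 80% target. Power survives.

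**4. Bias if the loss is informative.** Let p be the true absence rate in an arm, d the share of that arm lost and q the absence rate among those lost. The observed rate is (p − d·q)/(1 − d). The documents give neither d nor q, so both are assumed: q = 60% (twice the assumed control rate) and q = 45% (one and a half times).

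Worked example with q = 60%, 15% of controls lost and 5% of the intervention group lost:
- control: (0.30 − 0.15·0.60)/0.85 = 0.21/0.85 = 24.7%
- intervention: (0.15 − 0.05·0.60)/0.95 = 0.12/0.95 = 12.6%
- difference: 12.1 points, against a true 15

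| Lost, control / intervention | True rates | Observed, q = 60% | Difference, q = 60% | Difference, q = 45% |
|---|---|---|---|---|
| 10% / 10% | 30 v 15 | 26.7 v 10.0 | 16.7 | 16.7 |
| 15% / 5% | 30 v 15 | 24.7 v 12.6 | 12.1 | 13.9 |
| 5% / 15% | 30 v 15 | 28.4 v 7.1 | 21.4 | 19.5 |
| 15% / 5% | 30 v 30 | 24.7 v 28.4 | −3.7 | −1.9 |

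Differences are control minus intervention, in percentage points. The error can go either way, and it can create a difference where none exists. These scenarios show the mechanism; they do not forecast its size.

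**The case against.** The strongest defence is that the sentence is a retention measure. It directly follows the reminder procedure, whose stated purpose is retention and complete follow-up. For someone leaving the whole study, asking whether register follow-up may go on is proper and can save the primary outcome; a refusal must be respected. Entry consent and a later question do not strictly contradict each other. All of this stands for full withdrawal. It does not cover the person who only stops contact, whom the sentence includes by name.

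Three stronger readings are tempting, and the documents do not support them.

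- **Non-responders are dropped.** A reader might infer that anyone who does not reply loses SSIA follow-up. The text says participants are asked, not that they must approve, and gives no rule for silence. Someone who simply goes quiet has expressed no wish to withdraw, so the sentence does not reach them and their entry consent continues.
- **Healthcare-utilisation (VEGA) and medical-record data are lost.** The approval names only SSIA and the drug register, but collection from VEGA and the record is described without any withdrawal condition. Loss cannot be inferred from silence.
- **The loss can be counted from the sample size.** The step from 264 to 400 is described as summarising several calculations as well as allowing for dropouts, and these include sick days at about 75% power. It is not stated to be all dropout, so 34% is not a planned dropout rate, and no document gives a refusal rate.

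A fair further point is that withdrawal forms and levels of withdrawal usually sit in a full protocol or consent form not shown here. Their absence from an article is not the criticism. The criticism is that the rule the article does state merges two cases that need different handling.

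**Conclusion.** The point holds in a limited form. The plan takes consent to register data at entry and then asks for it again from people who wish to stop follow-ups only, without distinguishing them from those leaving the study. This puts the primary outcome and the drug-register outcome at avoidable risk of being missing, possibly unequally between arms.

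The size is unknown. Under the assumed loss patterns above, the observed difference ranges from 12.1 to 21.4 points around a true 15, and a null effect can appear as 1.9 to 3.7 points in favour of control. These figures depend wholly on the assumed loss and absence rates. Bias is the concern; power is adequate under every loss considered. The case for acting is that the exposure can be removed cheaply, not that serious loss has been shown.

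**What to change.** In Data collection, split the sentence into two rules.

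- Stopping treatment, texts or questionnaires does not end register follow-up. SSIA and drug-register data continue to 12 months under the entry consent unless the participant explicitly withdraws that consent.
- A participant who leaves the whole study is asked about register data, and a refusal is respected.

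Report by arm how many refuse register follow-up, so that readers can judge how far missing data could move the primary result.

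The cost is small: a wording change to the protocol and the withdrawal form, possibly with an ethics notification. Participants keep every right they have now. The gain is that the primary outcome is available for up to 200 per group, less only those who actively withdraw consent.

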### Statistical analyses

Primary outcomes are sickness absence and sick days, where the first outcome is binary and the second one is continuous and most likely skewed [47]. Sick leave regardless of reason will be retrieved. However, sick leave for diseases of the musculoskeletal system and connective tissue is of specific interest. Sample size calculations will be based on the general assumptions that we want a power of 80% and that statistical significance is set to α = 0.05. For the outcome sickness absence, the difference between the proportion of sickness absence = yes/no will be compared between the intervention (PREVSAM model) and control (TAU) group. We assume that approximately 30% in the control group will have sickness absence = yes at least one time during the 12 month follow-up period [48]. If the percentage of sickness absence = yes in the intervention group is assumed to be 15% or 20%, then the sample size in each group needs to be 312 individuals and 132 individuals, respectively. To detect a difference of 15% (30% with sickness absence in control group and 15% with sickness absence in intervention group), a total sample size of 264 (132 individuals in each group) would give approximately 80 cases to analyse for the primary outcome sick days. This would enable us to estimate 8 parameters in a logistic regression analysis. This would mean a power of about 75% to detect a difference of at least 0.6 Ln (sick days), if the standard deviation for Ln (sick days) is assumed to be 1. This is equal to a scenario with mean sick days of about 35 in the intervention group (PREVSAM model) and 68 in the control group (TAU). This would enable us to perform linear regression analysis adjusting for several covariates and estimating about 7 parameters. To summarise these calculations and allowing for dropouts, randomisation of 200 individuals to each group is required. An interim analysis will be performed for the primary outcome when 50% of patients have been randomised and have completed the 12 months follow-up. At the same time-point it might be possible to perform the short-term follow-up analyses. The interim analysis will be performed by a statistician, blinded to the treatment allocation. The statistician will report and discuss the results of the interim analysis with the steering committee in a joint meeting. The steering committee decides on the continuation of the trial.

Group characteristics will be presented as mean and standard deviations, median and 25th and 75th percentile or the number and percentage. For the primary outcomes descriptive analyses for sickness absence for the two groups will be presented according to recommendations [31]. The sickness absence will be presented with number of individuals who had sickness absence during the follow-up period. Proportions of individuals with sickness absence per month will be presented. The number of sick days (gross and net) with sickness benefit during the follow-up periods will be presented with mean and median values. For participation in work life additional measures will be presented with descriptive statistics regarding time to sick-leave spell for musculoskeletal pain. Number of days before a sick leave spell > 14 days occurs and number and duration of sick-leave spells per individual will be presented for gross and net days. Outcomes will be analysed according to intention-to-treat. Multivariable logistic regression analysis will be used for the primary outcome sickness absence during the follow-up period [1], not being sickness absent (0) adjusted for confounders. Multivariable linear regression analyses, or possibly quantile regression, will be used to evaluate differences between groups for sick leave days, among those have at least one sick leave spell. All other measurements will be analysed by calculating raw differences between baseline and follow-up assessments. Parametric and non-parametric tests will be used depending on data level and distribution. Sub-group analyses can be performed in regard to characteristics of interest, such as diagnosis or sick-leave. The level of significance is set to *p* < 0.05. Relevant statistical programs will be used for the statistical analyses, for example the IBM SPSS, SAS, STATA.

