**Methods:**

Eligible participants are adults who seek health care for musculoskeletal pain and who are at risk of developing persistent pain, physical disability, and sickness absence. Participants may be recruited from primary care rehabilitation centres or primary care healthcare centres in Region Västra Götaland. Participants will be randomised to treatment according to the PREVSAM model (intervention group) or treatment as usual (control group). The PREVSAM model comprises an interdisciplinary, person-centred rehabilitation programme, including coordinated measures within primary health care, and may include collaboration with participants’ employers. The primary outcome sickness absence is operationalised as the number and proportion of individuals who remain in full- or part-time work, the number of gross and net days of sickness absence during the intervention and follow-up period, and time to first sickness absence spell. Secondary outcomes are patient-reported short-term sickness absence, work ability, pain, self-efficacy, health-related quality of life, risk for sickness absence, anxiety and depression symptoms and physical disability at 1 and 3 months after inclusion (short-term follow-up), and at 6 and 12 months (long-term follow-up). A cost-effectiveness analysis is planned and drug consumption will be investigated.

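### The protocol contradicts itself on which sickness absence measure is primary, and its two modelled primaries share p < 0.05 without an order or success rule

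*Protocol article*

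**What the plan says.** The protocol article describes the primary outcome in several places.

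- **Abstract, Methods:** "The primary outcome sickness absence is operationalised as the number and proportion of individuals who remain in full- or part-time work", followed by gross and net days and time to first spell. The next sentence begins "Secondary outcomes are patient-reported short-term sickness absence, work ability, pain", so short-term self-report is secondary there.
- **Outcomes, Primary outcome:** three operationalisations. They are being on sickness absence and/or remaining in work, gross and net days, and time to first spell. The data are Swedish Social Insurance Agency (SSIA) spells longer than 14 days. On cause: "All sickness absence is planned to be analysed, but the main focus is on sickness absence relevant to musculoskeletal pain". The weekly text-message measure of shorter absence is described under the same heading.
- **Data collection:** "For the primary outcome sickness absence, data will be collected from the SSIA and self-reported short-term sickness absence will be collected weekly". Secondary outcomes follow in a separate paragraph.
- **Statistical analyses, first paragraph:** "Primary outcomes are sickness absence and sick days, where the first outcome is binary and the second one is continuous and most likely skewed". The sample size follows, with "we want a power of 80" per cent and "statistical significance is set to α = 0.05". An interim analysis of the primary outcome is also planned here.
- **Statistical analyses, second paragraph:** logistic regression for absence yes/no, and linear or possibly quantile regression for sick days among those with at least one spell. Time to a spell is an additional measure, reported descriptively. "The level of significance is set to" p < 0.05, for all outcomes alike.

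**The concern.** The first research question asks whether the model prevents sickness absence better than usual treatment. The protocol does not settle which result answers it.

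The definitions are not interchangeable. A person on part-time sick leave is absent and in part-time work at once. Table 1 admits people on unemployment benefits, student aid or parental leave, for whom remaining in work has no clear meaning. Participants are unblinded, so counting their text-message reports as primary would bring a different risk of bias into the main result.

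The two modelled primaries can also point in opposite directions. If the intervention mainly prevents short spells, mean days among the remaining cases could rise. No rule covers that result, or a significant result on only one of the two. The interim analysis, after which the steering committee decides on continuation, is tied to a primary outcome whose definition is not settled.

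**Working it through.** **1. The sections side by side**

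| Place | Primary outcome | Time to first spell | Text-message absence |
|---|---|---|---|
| Abstract, Methods | Remaining in work; gross and net days; time to first spell | Primary | Secondary |
| Outcomes, Primary outcome | Absence and/or remaining in work; gross and net days; time to first spell | Primary | Under this heading, but not one of the three listed items |
| Data collection | Sickness absence | Not mentioned | Grouped with the primary |
| Statistical analyses, paragraph 1 | Absence yes/no; sick days | Not mentioned | Not mentioned |
| Statistical analyses, paragraph 2 | Models for absence yes/no and sick days | Additional, descriptive | Not mentioned |

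The binary item, the status of time to first spell and the status of short-term absence each change between places.

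**2. The plan's own sample size**

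Inputs from Statistical analyses: 30% against 15%, power 80%, α = 0.05 (two-sided assumed; sidedness is not stated).

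n = [1.96·√(2·0.225·0.775) + 0.8416·√(0.30·0.70 + 0.15·0.85)]² / 0.15² = (1.157 + 0.489)² / 0.0225 ≈ 120.5, so 121 per group.

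With continuity correction: (120.5/4)·[1 + √(1 + 4/(120.5·0.15))]² ≈ 133.5, so 134 per group.

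The stated 132 is within two patients of the corrected figure. It uses the whole 0.05 for the yes/no outcome.

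Sick days, with about 80 cases taken as 40 against 40, difference 0.6 and SD 1 on the log scale: 0.6/√(2/40) = 2.683; 2.683 − 1.96 = 0.723; power Φ(0.723) = 76.5% (75.5% with the noncentral t). The stated value is about 75%, again at the full 0.05 and below the 80% target.

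**3. False-positive risk for the two modelled primaries**

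Sick days are compared only among people with a spell. With no effect on occurrence or duration, that test has its nominal level whatever the case counts, so it is nearly independent of the yes/no test. Hence 1 − 0.95² = 0.0975. A simulation of 4,000 null trials (132 per group, 30% absent, log-normal days with SD 1) gave 9.6%. If the two statistics were correlated, the figure would be 9.0% at 0.5 and 7.8% at 0.8. These correlations are assumptions; the document gives none.

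**4. More versions**

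Suppose yes/no and days are each tested for all causes and for musculoskeletal causes. Keeping yes/no and days independent, the risk runs from 9.75% if the two cause versions always agree to 1 − 0.95⁴ = 18.5% if they are independent. The document gives no figure that places the trial within this range.

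**5. Two ways to repair it**

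- Split α to 0.025 each: 30% against 15% needs 147 per group (160 continuity-corrected) instead of 121 (134). Power for yes/no is 75.4% with 132 per group, against 83.5% at 0.05, and 91.5% with 200. Sick-days power with 40 against 40 cases falls from 76.5% to 67.1%.
- Name one primary and order the rest: α stays 0.05 and the stated 132 per group stands.

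**The case against.** The strongest reply is that test order and α allocation commonly sit in a statistical analysis plan, which is not shown. That is fair, and their absence alone would be no finding. But this document does say which outcomes are primary, and its statements conflict. An analysis plan cannot carry out the primary analysis until they agree.

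Several stronger readings are tempting, and the text does not support them.

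- A reader might infer that every listed definition is tested at p < 0.05. Models are planned only for absence yes/no and sick days. Time to spell is descriptive, and remaining in work has no named test. A false-positive figure that counts a time-to-spell test would count something not planned.
- A reader might infer that only the yes/no outcome was considered in the sample size. Sick days are given about 75% power, and the 200 per group summarises both calculations.
- A reader might infer that text-message absence is declared primary. It is not among the three operationalisations, and the primary measures rest on registry spells over 14 days. What stands is its placement under the primary heading and its grouping under Data collection, against the abstract's secondary label.
- A reader might infer that the 30% refers to all-cause registry spells over 14 days. The sample-size text says only that absence occurred at least once. The stated main focus is musculoskeletal absence, so the cause is for the sponsor to choose.

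**Conclusion.** The point holds in this form: the sections contradict each other on the primary outcome, and the two primaries with planned models share one 0.05 level without an order or success rule. If success on either counts, the chance of at least one false positive is up to about 9.75%, before any effect of the interim look. This rests on two-sided tests at 0.05 and near-independence of the two tests, which follows from restricting sick days to those with a spell. Further versions by cause or by gross and net days would raise the risk, but the document does not say how many would be tested or how closely they agree. The matter should be settled before the interim analysis, because both that analysis and the answer to the first research question depend on it.

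**What to change.** Before the interim analysis:

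1. Name one primary outcome: SSIA-registered sickness absence, yes or no, over the 12-month follow-up. This is the outcome behind the 132 per group.
2. State its cause, all-cause or musculoskeletal, consistently with the stated main focus, and confirm that the assumed 30% refers to that definition.
3. State that the rule of spells longer than 14 days applies to all participants, including the unemployed, whose SSIA benefit starts on day two.
4. Make sick days (gross or net, specified) and the other-cause version secondary, in a fixed test order.
5. Remove remaining in work and time to first spell from the primary definition in the abstract and the Outcomes section. Both can still be reported descriptively.
6. Label text-message short-term absence secondary in the abstract, the Outcomes section and Data collection.
7. Say that the interim analysis uses the named primary.

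The cost is wording in the protocol and the trial registration, with no extra participants. The small downside is that a result on sick days alone could no longer support the primary claim. Keeping both as primary is possible, but it needs an explicit success rule; if either alone is to count, α must be divided, at the cost in size and power shown above.
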